## Abstract

**Background:**

It is estimated that seniors (≥65 years old) account for >50 % of acute inpatient hospital days and are presenting for surgical evaluation of acute illness in increasing numbers. Unfortunately, conventional acute care models rarely take into account needs of the elderly population. The failure to consider these special needs have resulted in poor outcomes, longer lengths of hospital stay and have likely increased the need for institutional care. Acute Care for the Elderly models on medical wards have demonstrated decreased cost, length of hospital stay, readmissions and improved cognition, function and patient/staff satisfaction. We hypothesize that specific Elder-friendly Approaches to the Surgical Environment (EASE) interventions will similarly improve health outcomes in a cost-effective manner.

**Methods/design:**

Prospective, before-after study with a concurrent control group. Four cohorts of 140 consecutively-screened older patients (≥65 years old) will be enrolled (560 patients in total). The EASE interventions involves co-locating all older surgical patients on a single unit, involving an interdisciplinary care team (including a geriatric specialist) in the development of individual care plans, implementing evidence-informed elder-friendly practices, use of a reconditioning program, and optimizing discharge planning. Subjects will be followed via chart review for their hospital stay, and will then complete in-person or telephone interviews at 6 weeks and 6 months after discharge. Measured outcomes include clinical (postoperative major in-hospital complication or death [primary composite outcome]; death or readmission within 30-days of initial discharge; length of hospital stay), humanistic (quality of life; functional, cognitive, and nutritional status) and economic (health care resource utilization and costs) endpoints. Within-site mean change scores will be computed for the composite primary outcome and the overall covariate-adjusted between-site pre-post difference will be the dependent variable analyzed using generalized linear mixed model procedures including adjustment for clustering.

**Discussion:**

Our findings will generate new knowledge on outcomes from acute surgical care in older patients and validate a novel elder-friendly surgical model including assessment of both clinical and economic benefits. If effective, we expect the EASE initiatives to be generalizable to other surgical centres.

**Trial registration:**

Clinicaltrials.govidentifier:NCT02233153

## Background

### Populations aging and current health care demands

The population of Canada, similar to that of many industrialized nations, is rapidly aging. Seniors (age ≥ 65 years) are anticipated to account for over a quarter of the Canadian population by 2040 [1]. Aging population demographics are expected to cause a marked increase in the prevalence of older patients with complex medical issues, frailty and dependence. Already, it is estimated that 85 % of older adults have at least one chronic health condition [2].

Currently in one province in Canada, seniors account for 63 % of acute inpatient days and 43 % of provincial health expenditure [3, 4]; this experience is common in other jurisdictions. Hospitalized seniors have higher rates of adverse events, surgical complications, and nosocomial infections than younger patients, which contributes to these high costs. They are at higher risk for hospital-acquired delirium, increased length of stay, readmission and loss of capacity to live independently [5–7]. One third of older adults develop new impairments in an activity of daily living during hospitalization and half of these are unable to recover this function [5, 6]. The Canadian health care system needs to adapt health service delivery models in order to meet the demands of our aging population.

### Acute surgery in older adults: challenges specific to this population

It is estimated that more than half of all operations are performed on patients older than 65 years of age. Approximately one third of these patients are discharged to an institutional care facility after major scheduled surgery [8, 9]. Older persons who present to hospital for surgery are often frail and have significant co-existing medical conditions [10], functional and cognitive impairment, limited support mechanisms, and a lower physiological reserve than younger patients. Because older patients are presenting for surgical evaluation of acute illness in increasing numbers, demand for surgical resources is also increasing [10]. Unfortunately, conventional acute care models rarely take into account the specific needs of this population; for example, proactive planning of services such as rehabilitation is seldom done [11]. Acute hospitals continue to be geared to provide care for those with single, acute illnesses rather than those with multiple acute and chronic conditions. Older adults present unique challenges due to comorbidity, cognitive and physical impairment, polypharmacy, and the need for functional rehabilitation and care to support discharge back to the community. Failure to consider these factors can result in poor outcomes, longer lengths of hospital stay and the greater need for institutionalization after surgery. This ultimately results in increased healthcare resource utilization.

Adverse outcomes in this group result from a complex interrelationship between baseline vulnerability and precipitating insults occurring during hospitalization [12]. Currently acute abdominal surgery is accompanied by many such insults that place older persons at particularly high risk for adverse events and functional decline, for example: fasting for gastrointestinal healing, addition of multiple drugs, immobility, nasogastric tubes, and bladder catheterization [12].

Delirium occurs as a common perioperative complication in older patients and is associated with significant adverse outcomes such as increased length of hospital stay, higher postoperative complication rates, falls, mortality and increased discharges to long term care [13, 14]. Delirium is also predictive of poor postoperative functional, cognitive and mobility recovery [15]. Delirium can be prevented using multi-component preventive strategies [14]. Part of this multi-component strategy can include regularly scheduled “comfort” rounds, which address unmet care needs and promote functional independence. Comfort rounds have been shown to improve patient experience in areas of pain management, comfort, and safety, and can reduce falls and pressure ulcers [16–19].

As many as 80 % of older hospitalized patients are either malnourished or at risk of malnourishment, and while in hospital they are at risk for further weight loss, which can lead to increased length of stay, long term care placement and death [20–22]. Adequate perioperative nutrition is of critical importance for patients who are malnourished prior to surgery. Recent studies suggest that earlier postoperative feeding is safe, supports quicker resumption of bowel function and reduces length of stay [23–26]. Functional decline, cognitive impairment and additional factors limiting food intake such as the effects of the underlying illness can further increase the risk for weight loss among older hospitalized patients [27]. Therefore, ensuring adequate access to and intake of food is important and can be achieved through structured processes that involve appropriate assistance with meals and ensuring adequate access to food and fluids [28, 29].

### Traditional surgical care vs. Elder focused surgical care

Standard hospital care can be risky for older people [12, 30–33] and is designed to deal with acute illness with expediency. Acute care surgery (ACS) is a surgical specialty that encompasses trauma and acute surgical disease (e.g. appendicitis, gallbladder inflammation, gastrointestinal obstruction, perforation and emergency cancer surgery) with the goal of providing optimal surgical care within the first 24 h of hospitalization. The ACS model has been embraced by many acute care sites as a means to decrease waiting times in the emergency department, as well as to improve the timeliness of surgery and operational efficiencies [34–36]. However, current ACS service delivery models do not take into account the unique characteristics and needs of the older population.

While specialized care for acutely ill older persons is not new, there is little evidence supporting models of geriatric care until the Acute Care for the Elderly model [37–39]. Originally developed to curb preventable functional decline experienced by older patients admitted to acute medical hospital wards, the Acute Care for the Elderly model emphasizes: (1) a specialized environment, (2) patient-centred care, (3) medical review, and (4) interdisciplinary team plans of care. The objective of elder-friendly hospital care was founded on gerontological principles such as screening for early identification of geriatric syndromes, family and caregiver involvement at all stages of care, interdisciplinary assessments, a holistic focus, respect for choices, and an environment supportive of discharge planning and community services [31]. Compared to traditional care, Acute Care for the Elderly models on medical wards have demonstrated decreased cost, length of hospital stay, readmissions, and improved cognition, function and patient/staff satisfaction [38–40]. To our knowledge, no prior study has developed an Acute Care for the Elderly model for elderly acute surgical patients.

For the reasons outlined above, studies assessing innovative ways to optimize care delivery in elders undergoing acute care surgery are urgently needed [41]. This is the first study to examine the impact of a novel care delivery redesign – Elder-Friendly Approaches to the Surgical Environment (EASE) - in elders receiving acute care surgery.

### Aim & objectives

The aim of the EASE study is to assess the impact of an elder-friendly surgical unit, with the goal of delivering evidence-informed care to improve the quality of care to older acute surgical patients, in order to reduce unnecessary health care resource utilization. The EASE study will realign current resources, implement evidence-informed practices, and improve health outcomes in a cost-effective manner.

The specific objectives of the EASE Study are to:Assess the clinical effectiveness of the EASE initiatives in reducing the rate of post-surgical complications, in-hospital mortality and length of stay, compared to controls.Determine if the EASE initiatives improves humanistic outcomes including health-related quality of life (HRQL), functional capacity and patient satisfaction, compared to controls.Determine the incremental cost and cost-effectiveness of the EASE initiatives.

In aggregate, these objectives will assess the program’s impact on a comprehensive range of outcomes important to patients, providers, and policy-makers.

## Methods

### Study design

This is a prospective, before-after study with a concurrent control group. Four cohorts of consecutively-screened older patients (≥65 years old) will be included:

Intervention Site (University of Alberta Hospital, Edmonton, Alberta Canada) (i)Hospitalized on the ACS service “before” or pre-EASE initiatives (140 participants)(ii)Hospitalized on the ACS service “after” or post-EASE initiatives (140 participants)

Control Site (Foothills Medical Centre, Calgary, Alberta, Canada)(iii)Hospitalized on the ACS service pre- EASE initiatives (140 participants, same enrollment period as (i) above)(iv)Hospitalized on the ACS service post- EASE initiatives (140 participants, same enrollment period as (ii) above)

Cohorts iii, and iv will serve as concurrent controls since the EASE initiatives will not have been implemented in that hospital. Of note, the ACS services at the intervention and control sites are structured similarly and admit similar patients.

### Subjects

Inclusion criteria (all criteria must be met):All patients ≥ 65 years oldIndex admission to ACS ServicePostoperative acute abdominal surgery

Exclusion criteria (any one sufficient to exclude):Elective general surgery casesPalliative surgery cases (surgery with the primary intention of improving quality of life or relieving symptoms caused by advanced non-curable disease)Trauma surgery casesNon-abdominal emergency surgery casesNursing home resident requiring full nursing care on admission (dependency in 3 or more activities of daily living)Patients from out of province, or transferred from another in-hospital inpatient service

### Interventions

The EASE initiative will involve:**Capacity re-alignment:** elderly surgical patients are currently scattered across different nursing units. Patients will be co-located on 1 unit to allow better implementation of the initiatives and coordination of care.**Interdisciplinary care delivery:** will include daily ward rounds by geriatric specialists, in addition to consultation with rehabilitation providers, pharmacists, dieticians and social workers within 24 h of admission to help in the development of individual care plans.**Implementation of evidence-informed practices:** optimizing evidence-based guideline adherence, such as:Medication review and reconciliationEarly mobilization on the surgical unitPrevention of postoperative complications (e.g. venous thromboembolism prophylaxis)Incorporation of Enhanced Recovery After Surgery program principles such as early feeding following surgery, reduced use of total parenteral nutrition, and avoidance or early removal of tubes [nasogastric, urinary catheters], drains, and lines [intravenous, central lines] [42].Elder-friendly practices such as comfort rounds, performed every 2 h by the nursing staff to address unmet care needs, mobility, nutrition, pain management, and prevention of falls and delirium.Health care provider/patient/family education**Reconditioning program:** a targeted, functional program that patients can perform independently at their bedside, beginning immediately post-operatively.**Transition optimization:** the interdisciplinary teams (from 2 above) will define the optimal blend of patient-specific services required to support safe, quality transitions to discharge with a goal to maximize functional recovery and return to baseline health status. This coordinated plan will be established at admission and will include appropriate discussions with the patients and caregivers.

### Data collection

Study personnel will collect data using standardized case report forms recorded on an electronic database using a secure, internet-based portal.**Socio-demographic information (baseline)**: including age, sex, ethnicity, body mass index, medical comorbidities, residence prior to admission, blood pressure, heart rate, respiratory rate, haemoglobin, creatinine and medication history. Data obtained from chart review will be used to create the Charlson comorbidity index [43] and Rockwood’s frailty index [44].**Hospitalization details (baseline):** including admitting diagnosis, operative procedure, operating surgeon, American Society of Anaesthesiologists Class, requirements for alternative service consults, total parenteral nutrition and urinary catheter utilization, discharge location, and any new requirement for alternative level of care upon discharge.**Major in-hospital complications (baseline):** all complications are defined using the Centers for Disease Control definitions [45], including:Intensive care unit admission (includes respiratory failure, cardiac arrest or septic shock),Vascular complications (myocardial infarction, stroke, deep venous thrombosis, pulmonary embolism)Serious infections (pneumonia, intra-abdominal abscess, urinary tract infection, deep wound infection or infected decubitus ulcer), andProtracted delirium (≥48 h). A validated chart-based method for identification of delirium will be utilized [46]. This chart-based instrument has a sensitivity of 74 % and a specificity of 83 %, using the Confusion Assessment Method [47] as the gold standard.**Mortality (baseline, 6 weeks, 6 months):** divided into in-hospital mortality, 30-day mortality and 6 month mortality.**Length of hospital stay (baseline):** divided into:acute length of stay defined as time until the acute medical treatment for that patient is complete;total length of stay which includes both medical treatment time and time awaiting transfer to another hospital (e.g., rural hospital) or alternative level of care (assisted living, long-term care placement or rehabilitation).**Readmission (6 weeks, 6 months):** divided into 30-day readmission and 6 month readmission.**Functional status (6 weeks):** including:Edmonton Frail Scale [48]: a valid and reliable tool to assess the frailty of the older patients. The scale has 11 items assessing cognition, general health status, functional independence, social support, medication use, nutrition, mood, continence and functional performance. Higher scores indicate greater frailty.Timed Up and Go [49]: a commonly used screening tool for falls risk. The patient is timed while they rise from an arm chair, walk three metres at a comfortable and safe pace, turn and walk back to the chair and sit down again. Faster time indicates a better functional performance.**Cognitive status (6 weeks):** using the Abbreviated Mental Test Score [50]. This 10 item test screens older patients for possible cognitive impairment, with lower scores indicating greater impairment.**Quality of life and health status (6 weeks and 6 months):**EQ-5D [51]: A widely used, validated, preference based generic HRQL instrument. It encompasses five domains of HRQL (mobility, self-care, usual activities, pain/discomfort, and anxiety/depression) and a visual analogue scale. The five health domains can be scored and totalled to yield a single Index (EQ-Index) score anchored between 0 (death) and 1 (full health). The visual analogue scale ranges from 0 to 100 with higher scores indicating better HRQL. The EQ-5D is also a measure of utility; a requirement for cost-effectiveness analyses.SF-12 [52]: A widely used, validated, generic HRQL instrument. It yields a physical and a mental health component summary score. Higher scores indicate better health status.**Nutritional status (6 weeks and 6 months):** using the Malnutrition Screening Tool [53]. This is a brief screening tool to assess nutritional status, with smaller scores indicating better nutritional status.**Health care resource utilization and costs (baseline and 6 months):** Health care resource utilization will be assessed through financial micro-costing databases. A modified health resource utilization questionnaire [54] will be administered at the final follow up visit to identify patient out-of-pocket expenses and indirect carer costs.

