
### Outcomes

The primary outcome from this study is the proportion of patients who experience a postoperative major in-hospital complication or death (composite outcome). Secondary outcomes include: the proportion of patients who experience each component of the primary composite outcome (in-hospital mortality, intensive care unit admission, vascular complications, serious infections, protracted delirium); the proportion of patients who die or are readmitted within 30-days of initial discharge; length of hospital stay; discharge location; requirement for an alternative level of care upon discharge; quality of life; functional, cognitive and nutritional status; and health care resource utilization and costs.

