### Data analysis

We will evaluate the effectiveness of the EASE initiative implementation by comparing between-site mean changes in each outcome in the cohort of patients hospitalized from the baseline cohort (defined as “pre-EASE”) to those hospitalized after implementation (defined as “post-EASE”).

Initially, exploratory data analysis will be performed on each major variable, including calculation of means, medians, proportions, and measures of central tendency. Baseline variables pre-EASE and post-EASE will be compared between sites using *X*^2^ tests for categorical variables, Student T-tests for normally distributed continuous variables, and the Wilcoxon rank sum test for non-normally distributed variables.

Secondly, within-site mean change scores will be computed for the composite primary outcome (difference of proportions) and the overall covariate-adjusted between-site pre-post difference (‘difference of differences’) will be the dependent variable analyzed using generalized linear mixed model procedures and will include adjustment for clustering by study site and operating surgeon. The regression model will be constructed using recommended techniques and assessment of model assumptions (including tests of normality, tests of colinearity and log-transformation of non-normally distributed continuous variables) will be performed as necessary. Additional adjustment for baseline age, sex, BMI, ethnicity, blood pressure, heart rate, respiratory rate, haemoglobin, creatinine, admitting diagnosis, medical comorbidities, operative procedure, Rockwood clinical frailty score, Charlson comorbidity index, American Society of Anaesthesiologists class, baseline month of enrolment, and/or baseline place of residence will be performed. Secondary endpoints will be analyzed as ‘difference of differences’ in a manner similar to that outlined for the primary outcome.

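### Timed Up and Go is defined only as a time and compared by means, so patients who cannot do the test have no place in the comparison, and restored mobility could dilute or reverse the apparent effect on this one secondary measure

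*Protocol article*

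**What the plan says.** Data collection lists functional status at 6 weeks only, measured by the Edmonton Frail Scale and Timed Up and Go. The second is described as a timed task: "The patient is timed while they rise from an arm chair, walk three metres at a comfortable and safe pace", then turn, return and sit. Its direction is fixed: "Faster time indicates a better functional performance". No category, score or rank is given for a patient who cannot complete it.

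The Outcomes section places "functional, cognitive and nutritional status; and health care resource utilization and costs" among the secondary outcomes. Functional capacity is also part of the second objective.

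Data analysis says EASE will be evaluated by "comparing between-site mean changes in each outcome". Secondary endpoints are handled as a difference of differences "in a manner similar to that outlined for the primary outcome", that is, with generalized linear mixed models. Model checking may include "log-transformation of non-normally distributed continuous variables".

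On the mode of follow-up, the abstract says subjects "will then complete in-person or telephone interviews at 6 weeks and 6 months after discharge". The ethics section joins the two modes with 'and' instead of 'or'.

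**The concern.** A time exists only for a patient who completes the test. Someone seen at 6 weeks who cannot get out of the chair or cover the distance is in the worst functional state, yet adds nothing to a mean of times. Log transformation changes the scale of the observed times and does not create the missing ones.

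EASE aims at mobility through early mobilization, comfort rounds and a bedside reconditioning program. It may therefore change who can be timed. A patient moved from unable to slow enters the post-EASE mean with a long time and pulls it in the unfavourable direction. Adjustment for baseline covariates does not reliably remove this, because ability at 6 weeks is itself a result of care. There is no earlier Timed Up and Go value to fall back on.

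The population makes inability plausible. Patients are 65 or older and have had acute abdominal surgery, and the only exclusion for dependency concerns nursing home residents needing full nursing care. The Background says that a third of hospitalized older adults acquire a new impairment in daily activities and that half of these do not recover.

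The point concerns patients who are followed up but cannot produce a time. It does not concern death, refusal or loss to follow-up.

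**Working it through.** The article gives no mean, standard deviation or inability rate for Timed Up and Go, so there is no planned figure to reproduce. All times and proportions below are assumptions. The control site is taken as unchanged, so the pre-post shift at the intervention site equals the difference of differences.

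**Step 1: one example.** Before EASE, 85 of 100 patients perform at a mean of 15 s and 15 cannot. After EASE, 7 of those 15 perform at 40 s each, and the other 85 are unchanged.

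- Mean before: 15.0 s.
- Mean after: (85 × 15 + 7 × 40)/92 = 1555/92 = 16.9 s.
- Apparent change: 16.9/15.0 = 1.13, a 13% worsening, while the share able rises from 85% to 92%.

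**Step 2: log scale.** Taking 15 s as the walkers' geometric mean, the ratio is exp[(7/92) × ln(40/15)] = 1.08, still about 8% in the wrong direction.

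**Step 3: what cancels it.** Let existing walkers improve by g seconds. The mean stays at 15 s when 85 × (15 − g) + 280 = 92 × 15 = 1380. This gives 15 − g = 1100/85 = 12.9, so g is about 2.1 s.

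**Step 4: range.** Let u_pre and u_post be the shares unable, t the time of newly mobile patients and g the gain in existing walkers. Then

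post mean = [(1 − u_pre)(15 − g) + (u_pre − u_post) t]/(1 − u_post).

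Shift from 15 s, in seconds (plus means apparently worse):

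| Unable, pre to post | g = 0; t = 25 / 35 / 45 | g = 1; t = 25 / 35 / 45 |
|---|---|---|
| 10% to 5% | +0.5 / +1.1 / +1.6 | −0.4 / +0.1 / +0.6 |
| 20% to 10% | +1.1 / +2.2 / +3.3 | +0.2 / +1.3 / +2.4 |
| 30% to 15% | +1.8 / +3.5 / +5.3 | +0.9 / +2.7 / +4.5 |

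With no gain in existing walkers, every entry points the wrong way. With a 1 s gain the shifts run from −0.4 to +4.5 s, so the sign depends on the assumptions.

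**Step 5: the same example ranked with 'unable' last.** Treat all 85 walkers as tied at 15 s. A random post-EASE patient beats a random pre-EASE patient with probability 0.15 × 0.92 = 0.138 and loses with probability 0.85 × 0.15 = 0.1275. The net is +0.0105 in favour of EASE. This is small, but the sign is right, and the share able (85% to 92%) shows the substance.

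**The case against.** The strongest reply is that the article does not say what a reader might infer from it. It nowhere states that Timed Up and Go is analysed in raw seconds or that patients unable to do it are dropped. The reference to mean changes covers all outcomes, including binary ones, and a generalized linear mixed model can take a binary or ordered response. A scoring rule for non-performers commonly sits in the analysis plan, and a code for inability may already be on the case report forms. Neither document is shown. This stands: the absence of a rule is not an error in itself. What remains is that the article defines the measure only as a time and names a comparison of means, and that combination suits this intervention poorly.

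The figures are assumed, and the example gives existing walkers no benefit although EASE is meant for everyone. This also stands, and limits the claim to what could happen.

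A reader might also infer that the whole functional result could point the wrong way. It could not on this ground. Timed Up and Go is one of two functional measures. Immobility still registers through the Edmonton Frail Scale's functional independence content, the EQ-5D mobility and self-care domains and the SF-12 physical score. The primary outcome comes from chart review.

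Finally, the abstract might be read as making telephone contact at 6 weeks a settled alternative, with the least mobile patients telephoned. The text does not establish that. The ethics section's wording fits in-person contact at 6 weeks and telephone at 6 months. So does the schedule, where the performance test is listed at 6 weeks only. Nothing says which patients would be telephoned.

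**Conclusion.** The point holds as a minor weakness in one secondary measure. Taken as written, a mean of times describes only those able to do the test, and EASE may enlarge that group. Restored mobility could then dilute the apparent effect or reverse it. In the worked example the shift is +1.9 s (13%; about 8% on the log scale). Across the assumed range it is +0.5 to +5.3 s with existing walkers unchanged, and −0.4 to +4.5 s if they gain 1 s. All of this rests on assumed inability rates and times, and on non-performers contributing no value, which is inferred from the definition of the test. The documents do not support saying that the plan discards these patients, that reversal is expected, or that the functional objective as a whole is compromised. Whether the 6-week contact may be by telephone is an ambiguity to reconcile, not a demonstrated loss of data.

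**What to change.** 1. On the case report form, record 'attempted but unable to perform' as a Timed Up and Go result, separately from 'not assessed', with the reason. State where a patient seen in person but too unsteady to attempt the test belongs.
2. In Data analysis, treat Timed Up and Go as an ordered outcome (bands of seconds with 'unable' as the worst category) or as ranks with 'unable' last. Keep the same site-by-period contrast.
3. Report the proportion able and the time among performers descriptively beside it.
4. Reconcile the abstract and the ethics section on whether the 6-week contact is in person. If a contact is by telephone, treat Timed Up and Go as not assessed for every such patient. Coding only the unable from self-report would add bad outcomes while able patients stayed missing, and would mix self-report with observed performance.

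The cost is two codes on a form and an ordinal or rank analysis in place of a mean. The downside is that the main effect is no longer expressed in seconds. The coding must be the same in all four cohorts, and inability not recorded at the visit cannot be recovered by a later analysis plan. Because enrolment began in April 2014, the forms already in use should be checked first.
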